#### Secondary outcomes

For the secondary outcomes, including the potential influence on abdominal pain, dyspeptic symptoms, health-related QoL, anxiety, depression, work absenteeism by parents, school absenteeism by children, somatisation and adequate relief, the Student’s t-test will be used for means of normally distributed data, the Mann-Whitney U test for non-parametric data and the χ^2^ test to compare proportions. To calculate the cost-effectiveness, cost–utility and cost-effectiveness ratios will be calculated for the extra costs per child with >50% reduction of symptoms of nausea and the extra costs per QALY.

As secondary analysis, the proportion of patients with >50% reduction of their nausea (severity, incidence and frequency) after treatment, 6 months’ and 12 months’ follow-up will be compared between groups using multivariate logistic regression correcting for age and centre.

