**Methods and analysis:**

To test efficacy, this multicentre, parallel, randomised controlled, open label trial evaluates whether gut-directed HT is superior to standard medical treatment (SMT) for reducing nausea. The study will be conducted at eleven academic and non-academic hospitals across the Netherlands. A total of 100 children (8–18 years), fulfilling the Rome IV criteria for chronic idiopathic nausea or functional dyspepsia with prominent nausea, will be randomly allocated (1:1) to receive HT or SMT. Children allocated to the HT group will receive six sessions of HT during 3 months, while children allocated to the SMT group will receive six sessions of SMT+supportive therapy during the same period. The primary outcome will be the difference in the proportion of children with at least 50% reduction of nausea, compared with baseline at 12 months’ follow-up. Secondary outcomes include the changes in abdominal pain, dyspeptic symptoms, quality of life, anxiety, depression, school absences, parental absence of work, healthcare costs and adequate relief of symptoms, measured directly after treatment, 6 and 12 months’ follow-up. If HT proves effective for reducing nausea, it may become a new treatment strategy to treat children with chronic functional nausea or functional dyspepsia with prominent nausea.

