**Figure 1 F1:**
[figure not shown]
Standard Protocol Items: Recommendations for Interventional Trials figure displaying the trial design and the outcome measurements. After screening for eligibility (T-1), children and parents sign the informed consent form and fill in the baseline questionnaire (T0). Children are then randomised in the hypnotherapy or standard medical treatment group. Assessments take place before the start of treatment (baseline; T0), 6 weeks after the start of treatment (T1), 3 months after the start of treatment (T2), 6 months’ follow-up (T3) and 12 months’ follow-up (T4).

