#### Secondary outcomes

In addition to the primary outcomes, the present study investigates secondary outcomes, including abdominal pain, dyspeptic symptoms, health-related QoL, anxiety, depression, school absences, parental absence of work and healthcare costs. Secondary outcomes are measured at 6 weeks and 3 months after treatment, and at 6 and 12 months’ follow-up after the end of treatment (figure 1).

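### The continuous secondary outcomes get unadjusted two-sample tests although a baseline questionnaire is completed at T0, which costs precision whether follow-up or change scores are tested

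*Protocol article*

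**What the plan says.** In the protocol article, Statistical analysis, Secondary outcomes, the rule for abdominal pain, dyspeptic symptoms, quality of life, anxiety, depression, absenteeism and somatisation is that the Student's "t-test will be used for means of normally distributed data, the Mann-Whitney U test for non-parametric data". Proportions get a χ² test. No covariate is named for the continuous scales.

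The one adjusted model in that section is a "multivariate logistic regression correcting for age and centre". It applies to the binary nausea response, and a baseline score is not among its covariates.

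The Figure 1 legend describes the collection at entry: "children and parents sign the informed consent form and fill in the baseline questionnaire (T0"), with randomisation following. It then lists assessments from T0 to T4.

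The abstract words the outcomes as changes: "Secondary outcomes include the changes in abdominal pain, dyspeptic symptoms, quality of life, anxiety, depression". The analysis section does not say whether the tests use changes or follow-up values.

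**The concern.** A score recorded before randomisation usually predicts the same child's later score. A comparison that conditions on it removes that predictable part from the error term. The article fixes two-sample tests that do not do this, so the choice is stated and not simply left open for an analysis plan.

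The Introduction gives directional hypotheses for pain, dyspepsia, quality of life, anxiety, depression and absence. The sample size rests on the binary nausea outcome alone. The secondary scales therefore have whatever power about 90 evaluable children provide, and an avoidable loss of precision makes an inconclusive result on them more likely.

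**Working it through.** **Inputs from the article.** Sample size calculation: 45 children per group, and 100 in total after 10% dropout, which checks as 90 / (1 − 0.10) = 100. Randomisation: 1:1. Statistical analysis: α = 0.05 for all analyses, sidedness not stated there. The article gives no SD, effect size or power for any secondary outcome, so there is no figure of its own to reproduce on this point.

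**Assumptions.** Equal SDs at baseline and follow-up; correlation r between them of 0.3, 0.5 or 0.7; a linear relation; a true effect of 0.5 SD of the follow-up score; a two-sided 5% test. None of these is in the documents.

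**Step 1: variances.** Take the variance of a t-test on follow-up scores as 1.

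- t-test on change from baseline: 2(1 − r)
- Linear model with treatment and baseline (ANCOVA): 1 − r²
- ANCOVA relative to the change-score test: (1 − r²) / [2(1 − r)] = (1 + r) / 2

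| r | Change / follow-up | ANCOVA / follow-up | ANCOVA / change |
|---|---|---|---|
| 0.3 | 1.40 | 0.91 | 0.65 |
| 0.5 | 1.00 | 0.75 | 0.75 |
| 0.7 | 0.60 | 0.51 | 0.85 |

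For any r between 0 and 1, both 1 − r² and (1 + r) / 2 are below 1, so ANCOVA is the more precise on either reading. At r below 0.5 a change-score test is worse than ignoring baseline altogether.

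**Step 2: power.** The standardised effect is 0.5 / √(variance ratio). For ANCOVA this is 0.5/√0.91 = 0.524, 0.5/√0.75 = 0.577 and 0.5/√0.51 = 0.700. For change scores it is 0.5/√1.40 = 0.423, 0.5/√1.00 = 0.500 and 0.5/√0.60 = 0.645. Two-sample t power at 45 per arm (the one degree of freedom spent on the covariate is ignored) is:

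| r | Follow-up t-test | Change-score t-test | ANCOVA |
|---|---|---|---|
| 0.3 | 65% | 51% | 69% |
| 0.5 | 65% | 65% | 77% |
| 0.7 | 65% | 86% | 91% |

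A normal approximation puts the follow-up test at 66% and ANCOVA at 70% / 78% / 91%, so the choice of formula does not matter.

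**Step 3: equivalent sample size.** Against the follow-up test, 90 / (1 − r²) gives 90/0.91 = 99, 90/0.75 = 120 and 90/0.51 = 176 children. An unadjusted follow-up comparison would need that many in total to match ANCOVA on 90.

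**The case against.** The strongest reply is that nothing here is an error. With 1:1 randomisation the planned tests are valid, the primary analysis stands apart, and the article promises no power for any secondary outcome. That is right, and it limits the point to lost efficiency. Calling the outcomes under-powered would measure them against a 0.5 SD target that the article never sets.

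The size also depends on the reading. If the abstract's changes are what is tested, baseline is already used. The gain at r = 0.7 is then about 5 percentage points (86% to 91%) and not 26 (65% to 91%), while at r = 0.3 it is 18 (51% to 69%). The article settles neither r nor the reading.

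A reader might infer more than the document supports:

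- **That every scale is measured at baseline.** The legend speaks of a baseline questionnaire in general. The scale-by-scale schedule would be in Figure 1, which was not available for this review, and the list that opens the Outcomes section on secondary outcomes omits somatisation.
- **That groups are compared separately at each visit.** The analysis text names no visits for these tests. This is an inference from the assessment schedule.
- **That chance baseline imbalance biases the results.** In a randomised comparison the standard error already allows for it. Nor does a condensed article that names no stratification factors show that none are used.
- **That the Mann-Whitney test yields nothing in scale units.** A Hodges-Lehmann shift with its interval can accompany it.

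Finally, the 1 − r² result belongs to a linear model. It may not carry over to absence hours, which are likely to be skewed with many zeros.

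What remains is that an unadjusted test is specified, a baseline measurement is described, and using it helps on both readings.

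**Conclusion.** The point holds as one of efficiency. As written, the continuous secondary outcomes are compared less precisely than the collected data appear to allow. At assumed correlations of 0.3 to 0.7, adjustment removes 9% to 49% of the variance of a follow-up comparison, or 35% to 15% of that of a change-score comparison.

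The direction needs only randomisation and a correlation between 0 and 1. The size rests on assumed values of r, equal SDs and, for the power figures, an assumed 0.5 SD effect. It applies to those scales that do have a T0 value. It does not touch the validity of the planned tests or the primary result. The change is worth making because it costs almost nothing.

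**What to change.** In Statistical analysis, Secondary outcomes, replace the unadjusted test for each continuous scale with a T0 value (abdominal pain, dyspepsia, KIDSCREEN-52, RCADS-25, and the CSI if it is collected at T0). Use a linear model with treatment and the baseline value of that scale at each follow-up time, and report the adjusted mean difference with its 95% CI. One mixed model over the visits is an acceptable alternative but is not needed to obtain the gain shown above. With baseline in the model, the treatment estimate is the same whether the outcome is entered as the follow-up value or as the change, so the ambiguity between abstract and analysis section disappears.

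Keep the Mann-Whitney test as a sensitivity analysis. For markedly skewed outcomes such as absence hours, use bootstrap intervals and do not count on the quoted gain. State how the model is combined with the multiple imputation that the article already plans.

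The cost is a few sentences and modest programming. No extra data or visits are needed.

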### Intervention

#### Hypnotherapy

Individual HT consists of six sessions of 50–60 min, given over a period of 3 months by a qualified hypnotherapist (weeks 1, 2, 3, 5, 7 and 11). Twelve hypnotherapist affiliated to the recruiting hospitals will offer the HT to children. All hypnotherapists have years of experience in performing HT in children. The hypnotherapists will use an adapted version of our previously used HT protocol.^13 20^ The HT protocol contains exercises focusing on normalisation of the gut motility, stress reduction and ego strengthening. The hypnotherapists will be instructed to use the same scripts, but are allowed to adapt the content to the child’s needs. The same protocol is used for children of all ages. However, the language used will be adjusted to the child’s developmental age.

In the first session, an introduction to HT will be given to the child and parents, including an explanation of what HT is and how it may help in reducing symptoms of nausea. Furthermore, the hypnotherapist will take a full history and children and parents are instructed to not talk about the nausea during the treatment period. The hypnotherapist will then start with a breathing exercise and introduce a progressive relaxation, in which children imagine floating on a big cloud. Positive suggestions to increase the child’s belly comfort will also be provided. For instance, the child will be instructed to make hands warm and place both hands on the belly, imagining warmth spreading through their abdomen and especially the stomach.

In the second session, the therapist will repeat the exercise on progressive relaxation. Additionally, the therapist will introduce an exercise focusing on reduction of anxiety and stress which is called ‘the favourite place exercise’.

The third session focuses on ego strengthening and a new exercise will be introduced: ‘the rainbow planet exercise’ for children attending primary school, and ‘the air balloon exercise’ for children in secondary school. In the first exercise, children choose a personal need from a rainbow that contains different needs, for example, a healthy stomach, courage, tranquillity or confidence.

In the fourth session, children are encouraged to release stress during the ‘the beach without worries exercise’ and additional ego strengthening suggestions are made.

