#### SMT+supportive therapy

In the SMT group, children will visit their treating paediatrician six times over a 3-month period. All paediatricians will be instructed to use the same protocol for treating symptoms of nausea. The protocol consists of a stepwise approach. In the first step, children and parents will be educated about CIN and FD, reassured that there is no structural organic underlying disease present, and dietary and lifestyle advices will be provided. Children will be advised to adhere to national practical guidelines for healthy eating by the Netherlands Nutrition Centre. Children will be recommended to avoid products containing caffeine, strong spices, citrus fruits, onions, fatty foods and, if applicable, to stop smoking. Additionally, the paediatrician will explore, together with children and parents, possible connections between stressful moments, emotional problems and complaints of nausea. If connections are present, the paediatrician will encourage children and parents to improve coping strategies to effectively manage stress, to reduce external stressors and to ensure an optimal environment with sufficient relaxation. Children will also be encouraged to continue their normal daily and sport activities and to go to school, to prevent or decrease avoidance behaviour.

In case this does not result in adequate relief of symptoms, the paediatrician continues with the second step. In the second step, proton pump inhibitors (PPI) in combination with domperidone will be prescribed. If this treatment is not effective in reducing symptoms the paediatrician continues with the third step which includes the prescription of ondansetron and (dis)continuation of PPIs. If again no adequate improvement occurs, in the fourth step, Iberogast will be started for children >12 years. If children do not respond to Iberogast (>12 years) or ondansetron (<12 years), the paediatrician will continue with the fifth step and prescribe erythromycin. Finally, if previous treatment did not prove to be successful in reducing symptoms, cyproheptadine will be prescribed.

The paediatrician will evaluate each step after two to 4 weeks. All dosages, except for Iberogast, will be prescribed according to www.kinderformularium.nl (Dutch medical guideline for paediatricians).

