In addition to the medical treatment, children will receive six half hour sessions of supportive therapy given by the treating paediatrician. In these sessions, the symptom progression will be discussed and patient education will be provided. Moreover, exploration of potential contributing triggers (ie, dietary product, emotional problems and stressful events) will be evaluated together with children and parents. Supportive therapy is added to correct for the patient-therapist time in the HT group.

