The study has several strengths. The first strength is that paediatricians from eleven different hospitals throughout the Netherlands will recruit all children and adolescents. The hospitals, both an academic centre and teaching hospitals, serve an ethnic and socio-economic diverse population of children and adolescents. This recruitment method has two advantages: first, it may reduce response bias to the intervention. It has previously been reported that patients from primary and secondary level care may have different responses to treatment.^38^ All children included in the present study receive secondary level care. The second advantage is that the multicentre design of the study will increase generalisability of the trial outcomes.

Another strength of the study is the long-term follow-up of 1 year which allows us to properly compare the potential effectiveness of HT with SMT. It has been known that the severity of functional gastrointestinal symptoms in children varies over time^39^ and a continuous improvement in symptoms is often reported in children receiving HT.^13^

This study also has several limitations. The first limitation is that children, parents, investigators and healthcare providers are not blinded for the received treatments, which is not possible due the nature of HT. Several solutions will be applied to limit the risk of bias. First, to minimise performance bias, paediatricians and hypnotherapists will follow treatment guidelines to prevent any use of additional or alternative forms of care during the study period that may influence treatment outcomes. Second, to reduce the risk of detection bias, children and adolescents use reliable outcome measures and record symptoms themselves at home. Moreover, children and adolescents record symptoms of nausea for seven consecutive days, which corrects for individual variability of symptoms over time. Third, the endpoints of the study are preregistered.

The second limitation is that the SMT provided by paediatricians in this study may not reflect usual clinical practice. In the present study, children and adolescents receive longer and more intensive medical therapy from their paediatrician compared with the real medical practice situation. However, previous studies indicate that patient-provider interactions can largely influence gastrointestinal treatment outcomes.^40^ Therefore, it is important to control for the time spent per patient in the SMT group.

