If the results of this study show that HT given by a therapist is comparable or slightly more effective than medical treatment provided by paediatricians, HT may become a new treatment strategy to help children with CIN or FD. Furthermore, as HT is presumably less costly than treatments by a specialist it may also decrease healthcare costs.

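### The planned cost ratios charge SMT for paediatrician sessions added as an attention control, with no allowance for that time when the result is read as a saving over usual care

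*Protocol article*

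**What the plan says.** Under Statistical analysis, Secondary outcomes, the protocol article plans ratios for "the extra costs per child with >50% reduction of symptoms of nausea and the extra costs per QALY". It does not say how paediatrician contact in the SMT arm is to be costed.

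The section on SMT plus supportive therapy says that "children will visit their treating paediatrician six times over a 3-month period" and that, on top of the medical treatment, "children will receive six half hour sessions of supportive therapy given by the treating paediatrician". The reason given is that "Supportive therapy is added to correct for the patient-therapist time in the HT group".

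The Hypnotherapy section reads: "Individual HT consists of six sessions of 50–60 min, given over a period of 3 months by a qualified hypnotherapist". The Co-interventions section then has HT children see their paediatrician for an evaluation after the sixth session, with further medical treatment if needed.

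The Discussion lists as a limitation that "the SMT provided by paediatricians in this study may not reflect usual clinical practice", and explains that "children and adolescents receive longer and more intensive medical therapy from their paediatrician compared with the real medical practice situation". It defends this as control of contact time, because provider contact can influence outcome, and does not mention costs. The Introduction expects lower healthcare costs in the HT group than in the medical treatment group. The Discussion ends by suggesting that "as HT is presumably less costly than treatments by a specialist it may also decrease healthcare costs".

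**The concern.** An attention control serves the efficacy comparison: if both arms get comparable contact, a difference in response is easier to credit to hypnosis. For costs, the same feature works in the other direction. Paediatrician time supplied because of the trial becomes a resource used by SMT and apparently saved by HT. The HT therapist hours are the intervention itself and would also be needed in practice, so the distortion falls on one arm only.

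At stake is the step from the trial to practice. The final paragraph of the Discussion would consider HT a new strategy even if it proves only comparable or slightly better. In that case cost carries much of the argument for adoption, and cost is the quantity that the added sessions move.

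**Working it through.** The plan gives no cost figure to reproduce. The article also gives no unit costs, no length for the SMT medical visit and no usual-care visit frequency. The size is therefore shown over assumed ranges, on contact time alone.

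**Inputs from the article**
- Supportive sessions: 6 × 30 min = 180 min = 3 paediatrician hours per SMT child.
- SMT visits: 6 in 3 months, length not stated. Assumed length *v*: 10, 15 or 20 min.
- HT: 6 × 50 to 60 min = 300 to 360 min = 5 to 6 therapist hours.
- Expected response (Sample size calculation): 80% with HT, 50% with SMT, a difference of 0.30.

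**Break-even.** Let *r* be the therapist's hourly cost divided by the paediatrician's. On contact time, HT is cheaper when *r* × HT hours is below SMT hours, so break-even is *r* = SMT hours / HT hours. SMT hours are 6*v*/60 plus the supportive hours that are counted (3, 1.5 or 0).

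| *v* | SMT hours: all / half / none of the sessions | Break-even, all | Break-even, half | Break-even, none |
|---|---|---|---|---|
| 10 min | 4.0 / 2.5 / 1.0 | 0.67–0.80 | 0.42–0.50 | 0.17–0.20 |
| 15 min | 4.5 / 3.0 / 1.5 | 0.75–0.90 | 0.50–0.60 | 0.25–0.30 |
| 20 min | 5.0 / 3.5 / 2.0 | 0.83–1.00 | 0.58–0.70 | 0.33–0.40 |

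In each range the lower value is for 6 HT hours and the upper for 5.

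**Where the sign reverses.** With all sessions counted, HT is cheaper everywhere in the table if *r* is below the smallest break-even, 4.0/6 = 0.67. With none counted, HT is dearer everywhere if *r* is above the largest, 2.0/5 = 0.40. For *r* of about 0.40–0.67 the sign therefore reverses under every assumed combination. If only half the sessions are removed, no value of *r* reverses throughout, because it would have to lie above 0.70 and below 0.67. At *v* = 15 min alone, reversal then holds for *r* of 0.60–0.75.

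**If the half hour is the whole visit.** The article also describes six sessions of SMT plus supportive therapy, which allows this reading. SMT is then 3 hours and break-even is 3/6 to 3/5 = 0.50–0.60. Against routine visits of 10–20 min (1–2 hours, break-even 0.17–0.40), the excess is only 1–2 hours, and the sign reverses throughout for *r* of 0.40–0.50.

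**Cost per extra responder.** If 3 hours are removed and response is held, the ratio shifts by 3/0.30 = 10 paediatrician hours per extra responder.

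**Why the ratio's direction is less certain.** Let *D* be the as-delivered cost difference and *E* the excess, both in paediatrician hours. Suppose SMT response without the extra attention were 25% (an assumption), so that the difference in response becomes 0.55. The usual-care ratio (*D* + *E*)/0.55 falls below the as-delivered ratio *D*/0.30 when *D* > 0.30*E*/(0.55 − 0.30) = 1.2*E*. For *E* = 3 this needs *D* > 3.6, and for *E* = 1.5 it needs *D* > 1.8. On the whole-visit reading with *r* = 1 and 6 HT hours, *D* = 6 − 3 = 3. With *E* = 1.5 (15-min routine visits), the as-delivered ratio would then understate HT's value against usual care.

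**Left out.** Drugs in the SMT steps, the HT evaluation visit and any added treatment, and parental costs are not counted. Charging HT one 15-min paediatrician visit at *v* = 15 changes break-even to (4.5 − 0.25)/6 to (4.5 − 0.25)/5 = 0.71–0.85 with the sessions, and to 1.25/6 to 1.25/5 = 0.21–0.25 without.

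**The case against.** The strongest reply is that the article names two ratios and no costing rule. A full protocol or analysis plan may define the cost items and exclude the supportive sessions, in which case the shift disappears. This stands as a limit, and the conclusion is conditional on the sessions being costed as delivered. It does not remove the point, which rests on what is stated: a comparator acknowledged to exceed practice, cost ratios planned against it, and a remark about healthcare costs in general.

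A second reply is that the limitation is already disclosed. It is, but only as a matter of treatment intensity and outcome, with no link to costs.

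A third is that some of the supportive content (education, exploring triggers and stress) overlaps the first step of the medical protocol and may occur in ordinary visits. This also stands. A reader might infer that no child in routine care would receive any of this time. The article says only that trial care is longer and more intensive, so 3 hours is an upper bound.

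A reader might also infer that the trial is set to conclude that HT saves money. The Introduction states a hypothesis about the two trial arms and the Discussion is hedged, so neither is a decision rule.

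**Conclusion.** The point holds as a limit on what the cost results can say about practice. If the supportive sessions are costed as delivered, the cost difference favours HT, relative to usual care, by up to 3 paediatrician hours per child. On contact time alone, with separate visits of 10–20 min and all six sessions removed, that is enough to reverse the sign for hourly cost ratios of about 0.40–0.67. The size rests on assumed visit lengths and on an unknown share of the sessions being due to the trial.

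Two stronger readings are not supported. A reader might infer that the cost analysis is invalid, but the ratios remain valid for HT against SMT as delivered. A reader might also infer that both ratios are biased towards HT. That direction follows for the cost difference only, because the extra contact may raise SMT response and shrink HT's incremental effect. Nor is a sign reversal shown for total costs, since drugs, the evaluation visit and parental costs are not in the calculation.

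This concerns a secondary objective and does not touch the primary comparison. It is cheap to settle before the data are seen.

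**What to change.** Add to Statistical analysis, Secondary outcomes, a pre-specified sensitivity scenario in which the protocol-driven supportive sessions are taken out of SMT costs. Run it once with all six removed and once with a stated partial share, since some of this time may occur in routine care. Report it beside the as-delivered result, and state that SMT response is held unchanged, which makes the scenario conservative for HT.

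Describe the as-delivered ratios as HT versus intensified SMT, extend the limitation in the Discussion to costs, and word the closing remark on healthcare costs in light of both results.

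The scenario needs only visit data and changes nothing in treatment. The cost is one extra analysis and a cost claim that may turn out less favourable to HT.

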### Recruitment

#### Recruitment procedures

Children and adolescents will be recruited in outpatient paediatric clinics of 1 academic and 10 non-academic hospitals in the Netherlands: Amsterdam University Medical Center (Amsterdam), Amphia Hospital (Breda), Maxima Medical Center (Veldhoven), Northwest Clinics (Alkmaar), Maasstad Hospital (Rotterdam), Zuyderland Medical Center (Heerlen), Rijnstate Hospital, (Arnhem), Haaglanden Medical Center (Den Haag), Spaarne Hospital (Hoofddorp), Isala Clinics (Zwolle) and St. Antonius Hospital (Nieuwegein). These centres are located in both urban and rural areas throughout the Netherlands, serving an ethnically diverse paediatric population.

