### Sample size calculation

The primary outcome of the RCT is the proportion of patients with at least 50% reduction of their symptoms of nausea compare to baseline at 12 months follow-up. Based on our pilot study ([name] ‘A pilot-study of hypnotherapy as a treatment for functional nausea in children’) and the success percentages in studies using HT in adults with FD^35^ and in paediatric patients with cancer,^14^ we expect that 80% of the children in the HT group will have >50% reduction of their symptoms of nausea after 1 year. In the SMT group, we anticipate that 50% of the children will have >50% reduction of their symptoms of nausea after 1 year. Based on these expected proportions, 45 children per group will be needed to achieve a power of 80% with a one-sided significance level of 5%. Accounting for a 10% dropout, 100 children will be included in this study. If a child is prematurely withdrawn from the study, he/she will not be replaced; data will be analysed according to the intention to treat (ITT) analysis.

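### If centre enters the secondary logistic regression as ordinary indicator terms, 11 centres against 32–35 expected non-responders would inflate a true odds ratio of 4 to about 5

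*Protocol article*

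**What the plan says.** Under Statistical analysis, Secondary outcomes, the protocol article plans a comparison of responder proportions that "will be compared between groups using multivariate logistic regression correcting for age and centre". It covers three occasions: "after treatment, 6 months’ and 12 months’ follow-up will be compared between groups". Under Recruitment procedures, children come from "outpatient paediatric clinics of 1 academic and 10 non-academic hospitals in the Netherlands", which makes 11 centres.

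The expected response is given under Sample size calculation. For hypnotherapy (HT): "we expect that 80% of the children in the HT group will have >50% reduction of their symptoms of nausea after 1 year". For standard medical treatment (SMT): "we anticipate that 50% of the children will have >50% reduction of their symptoms of nausea after 1 year". The target is 45 children per group, and the total follows from it: "Accounting for a 10% dropout, 100 children will be included in this study".

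The article does not say whether centre is a fixed or a random effect, makes no provision for small centres, and gives no expected centre sizes. The randomisation section describes varying blocks and does not mention stratification by centre. The primary analysis is an unadjusted chi-square test.

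**The concern.** In a logistic model, the information is limited by the rarer outcome, here non-response. Naming centre beside age ordinarily means entering it as a categorical covariate. With 11 centres, that spends ten coefficients on nuisance terms, each estimated from eight or nine children. Maximum-likelihood log odds ratios are then biased away from zero, including the one for treatment. A centre in which every child responds, or none does, has no finite coefficient of its own, and its children add nothing to the treatment comparison.

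At stake is the size of a reported effect. This is the only adjusted comparison of responder status that the article describes. Under the trial's own assumptions its odds ratio would overstate the benefit of HT.

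**Working it through.** **Inputs from the article.** 11 centres; expected response 80% (HT) and 50% (SMT) at 12 months; 45 per group, 100 enrolled.

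**The plan's own figures.** With 80% power, n per group for 80% versus 50% is 31 (one-sided 5%), 37 (one-sided, continuity-corrected), 39 (two-sided 5%) and 45 (two-sided, continuity-corrected). The stated 45 therefore reproduces on the last basis, although the article calls the test one-sided. That is a separate matter and does not affect this point. The total reproduces: 90 / 0.9 = 100.

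**True odds ratio implied.** (0.8/0.2) / (0.5/0.5) = 4.0.

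**Non-responders at 12 months.** 45 × 0.2 + 45 × 0.5 = 31.5 with 90 analysed; 50 × 0.2 + 50 × 0.5 = 35 with 100 analysed.

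**Coefficients if centre is a set of indicators.** Treatment 1 + age 1 + centre 10 = 12. Non-responders per coefficient: 31.5/12 = 2.6 and 35/12 = 2.9. Children per centre if equal: 90/11 = 8.2 and 100/11 = 9.1.

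**Simulation.** 2,500 trials per scenario, true odds ratio 4.0, 1:1 allocation in blocks of 2, 4 and 6, not stratified by centre. Age has no effect on outcome. The article gives no centre sizes or heterogeneity, so these are assumptions: centres equal, moderately uneven (largest about 20% of children, smallest about 3%) or skewed (about 35% to 2%); centre SD on the logit scale 0 or 0.5.

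| N | Centre sizes | Centre SD | Trials with a one-outcome centre | Median OR, centre indicators + age | Median OR, age only |
|---|---|---|---|---|---|
| 90 | equal | 0 | 29.5% | 5.14 | 4.18 |
| 90 | equal | 0.5 | 42.1% | 5.20 | 3.97 |
| 90 | moderate | 0 | 63.0% | 5.07 | 4.13 |
| 90 | moderate | 0.5 | 69.2% | 5.15 | 3.95 |
| 90 | skewed | 0 | 86.0% | 5.04 | 4.18 |
| 90 | skewed | 0.5 | 91.0% | 5.02 | 3.88 |
| 100 | equal | 0 | 19.6% | 4.92 | 4.11 |
| 100 | equal | 0.5 | 33.0% | 5.06 | 3.88 |
| 100 | moderate | 0 | 54.4% | 4.93 | 4.18 |
| 100 | moderate | 0.5 | 64.7% | 4.88 | 3.88 |
| 100 | skewed | 0 | 84.9% | 4.91 | 4.15 |
| 100 | skewed | 0.5 | 88.5% | 5.01 | 4.02 |

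- **Bias.** Medians in the table run from 4.88 to 5.20. Repeat simulations widen this to about 4.5–5.2, that is 4.5/4.0 = 1.13 to 5.2/4.0 = 1.30. Averaged on the log scale, the table's scenarios give 4.99–5.43, or 25–36% too high. The inflation is present with equal centres and SD 0, where no real centre effect exists. It is therefore small-sample bias, and not the usual gap between a centre-specific and a population-average odds ratio.
- **Interval coverage.** 92.6–94.1% for a nominal 95%.
- **Type I error.** With 65% response in both arms, N = 90 and equal centres (4,000 trials), the centre-indicator model rejects in 6.9% (Wald) and 7.5% (likelihood ratio), against 5.0% and 5.6% with age only. Other runs gave Wald rates down to 5.4%.
- **One-outcome centres, hand check.** For equal centres of eight children at 65% overall response: 1 − (1 − 0.65^8 − 0.35^8)^11 ≈ 30%, in line with the first row. Across all runs the range was about 17–43% for equal centres.
- **Is the treatment odds ratio lost?** It was not finite in only 0–3 of 2,500 trials per scenario.

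**Alternatives, true odds ratio 4.0.** Firth-penalised 3.97–4.26; conditional on centre (age omitted) 4.06–4.39; both are log-scale averages from 500 trials per scenario. Further runs gave 3.8–4.4 for a random centre intercept and 3.9–4.2 for Mantel-Haenszel by centre.

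**The case against.** The strongest objection is that the article never says centre is a fixed effect. A random intercept, a conditional or penalised fit, or pooling of small centres would all satisfy the same sentence, and such detail often sits in an analysis plan, which is not shown here. This stands as a limit: the finding is conditional on the natural reading. It does not remove the point, because the sentence does fix centre as an adjustment variable, and its ordinary implementation is the one that performs badly.

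It is also fair that the analysis is secondary, that age and centre are defensible adjusters in a multicentre trial, and that the outcome is already relative to each child's baseline. Leaving out baseline score and diagnosis is thus not an error; adding them is an improvement.

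Stronger readings that a reader might infer are not supported:

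- That the model would often fail. One-outcome centres are common, but the treatment odds ratio remains estimable almost always.
- That the trial's main conclusion is at risk. The primary chi-square test and the sample size contain no centre terms, and no section says this regression is meant to support the primary result.
- That the 32–35 count holds at every occasion. The article gives response rates for 12 months only.

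**Conclusion.** The point holds in conditional form. If centre is entered as indicator terms by ordinary maximum likelihood, the secondary 12-month odds ratio would be reported at about 5 when the truth under the trial's own assumptions is 4, with slightly raised type I error. The bias does not depend on the unknown centre sizes. The frequency of one-outcome centres does: about 17–43% of trials with equal centres, and roughly 54–91% under the assumed uneven ones. In those trials some children drop out of the comparison, but the analysis can still be done.

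The result rests on the 80% and 50% response rates, on all 11 centres recruiting, and on 90–100 children analysed. No figure can be given for the two earlier occasions. The plan should settle this before analysis, but it is a matter of how large a secondary effect looks, not of whether the trial is valid.

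**What to change.** State how centre enters. Use a logistic model with a random centre intercept in place of fixed centre indicators; a conditional logistic model stratified by centre, or a Firth-penalised model, is an acceptable alternative. Keep age. Add the baseline nausea score from the 7-day diary, naming which of its three scores is used, and preferably diagnosis (chronic idiopathic nausea or functional dyspepsia). Use the same model after treatment and at 6 and 12 months.

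With treatment, age, one baseline score and diagnosis, the random-intercept model has four covariate coefficients, or 31.5/4 = 7.9 to 35/4 = 8.8 non-responders each. The simulations above did not include baseline score or diagnosis, so they support the handling of centre and not the size of any gain from those two terms.

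A Mantel-Haenszel odds ratio stratified by centre is a useful check, but it cannot also carry age, baseline score and diagnosis in strata of eight or nine children.

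The cost is a small change of wording for a secondary analysis. The extra covariates are already collected at entry, and the primary test and sample size stay as they are.
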